#### Sample size justification

The sample size for the quasi-experiment was calculated using the G * Power 3.1 sample size calculator software (Faul et al., 2009). Based on expected changes in the FRS with a medium effect size of 0.25, the minimum number of participants required in each intervention and control group is 28, giving this study 80% power at a significance level of 0.05 (two-tailed test). Considering the prospective nature of the study and attrition rate of 20%, a minimum number of 34 participants will be recruited into each study group.

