**Methods::**

A minimum total sample of 68 low-income community members at risk for CVD will be recruited and allocated either to the control group or the intervention group. Participants in the control group will receive standard lifestyle advice and printed materials for CVD prevention, while the intervention group will participate in the 8-week MYCardio-PEER intervention program. The participants will be assessed at Week 0 (baseline), Week 8 (post-intervention) and Week 20 (post-follow-up).

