### Participant allocation

Two groups will be under study for this quasi-experiment: the intervention group and the control group. The recruited participants will be allocated into one of the two groups based on their geographical location to ensure participants’ convenience when participating in the intervention activities. The participants in the intervention will be further divided into five subgroups, each consisting of six to seven members based on their peer connectivity. The non-random allocation considers familiarity and peer support, which are expected to lead to higher engagement levels in the intervention activities, promoting better adherence to the intervention and potentially more significant lifestyle behavioural changes.

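### The recruitment minimum of 34 per group does not preserve the required 28 at the stated 20% attrition; 35 would be needed

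*Protocol article*

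**What the plan says.** The Sample size justification section of the protocol article fixes three numbers.

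- The evaluable requirement, tied to 80% power at a two-sided 5% level: "the minimum number of participants required in each intervention and control group is 28".
- The loss allowance, given as the reason for recruiting more than that: "Considering the prospective nature of the study and attrition rate of 20"%.
- The resulting recruitment figure: "attrition rate of 20%, a minimum number of 34 participants will be recruited into each study group".

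The Methods paragraph of the Abstract gives the corresponding total: "A minimum total sample of 68 low-income community members at risk for CVD will be recruited". No inflation formula is printed in either place. The Participant allocation section divides the intervention group into five subgroups of six or seven people, which spans 30 to 35. It gives no other sample size figure.

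**The concern.** An attrition allowance exists so that the required number is still available after the assumed loss. The recruitment figure should therefore be the required number divided by the proportion expected to remain. Here it looks as if 20% of the required number was added instead. Adding 20% and then losing 20% does not return to the starting number, because the loss applies to the larger, recruited number.

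What is at stake is whether the published recruitment target does what the text says it does. If recruitment stopped at the minimum and attrition were as assumed, each group would finish below the number that the protocol itself calls the minimum.

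**Working it through.** **Inputs.** Required per group, n = 28; attrition, a = 0.20; recruitment minimum, 34 per group (all from Sample size justification). Total minimum, 68 (Abstract, Methods). Two groups of equal size.

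**Reproducing the printed figure.** n × (1 + a) = 28 × 1.20 = 33.6, rounded up to 34 per group; 2 × 34 = 68. This matches both printed numbers exactly.

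**Figure that keeps 28 after 20% loss.** n / (1 − a) = 28 / 0.80 = 35.0 per group; 2 × 35 = 70. The division is exact, so no rounding choice leads from 35 to 34.

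**What 34 leaves.**

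| Recruited per group | Expected to remain at 20% loss | Required |
|---|---|---|
| 34 | 34 × 0.80 = 27.2 | 28 |
| 35 | 35 × 0.80 = 28.0 | 28 |

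In total, 68 × 0.80 = 54.4 against 2 × 28 = 56.

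**Attrition that 34 tolerates.** 1 − 28/34 = 6/34 = 17.6%. Six losses leave 28. A seventh (7/34 = 20.6%) leaves 27.

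**Size in power terms.** The article does not name the test family, the effect-size metric or the within-person correlation behind the 28, so the power at 27 cannot be computed from its stated inputs. As an assumption, take a two-sided two-sample t-test at 5% and choose the standardised difference so that 28 per group gives exactly 80%. That difference is d = 0.762, a back-solved value that does not appear in the protocol. With it, power is 0.800 at 28 per group and 0.785 at 27, a loss of 1.5 points. The normal approximation, calibrated the same way (d = 0.749), gives 0.800 and 0.786.

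**The case against.** The best defence is that 34 and 68 are both worded as minimums. They are floors, so the study may recruit more, and 35 already fits the planned subgroups in the intervention group. This stands as a limit on the consequence. A reader might infer that the trial is bound to miss 80% power, but the document does not support that: the shortfall requires recruitment to stop at the floor and attrition to reach the assumed rate. It does not rescue the figure itself. The article presents 34 as the result of allowing for 20% loss, and as that result it is one too low.

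A second objection is that the power loss is not established. This also stands. The protocol quotes an effect size of 0.25 and plans a repeated-measures ANCOVA, whereas the 78.5% comes from a t-test with a back-solved difference. Suppose instead that the 0.25 is Cohen's f, with three assessments, a within-person correlation of 0.5 and sphericity. A total of 54 then gives about 0.98 power for the group-by-time interaction, against about 0.99 at 56. For the between-group effect the figures are about 0.60 and 0.61. In neither case does 27 versus 28 per group decide the power. Whether 28 is the right base number is a separate question. The attrition step is wrong for whatever base is used.

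A third objection is that multiplication is only inferred. That is correct, although 28 × 1.20 rounded up gives the printed value exactly. The inconsistency does not depend on the inference: however 34 was reached, 20% loss leaves fewer than 28.

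The subgroup plan settles nothing either way. Five groups of seven make 35; four of seven and one of six make 34.

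**Conclusion.** The point holds as a minor correction to a stated sample size figure. Taking the protocol's 28 per group and 20% attrition as given, the minimum of 34 per group and 68 in total falls short by one participant per group, two in total. It tolerates 17.6% attrition instead of 20%. The power cost is about 1.5 points, and only on the assumption that 28 gives exactly 80% under a two-sample t-test. The arithmetic is certain, the multiplied allowance is a strong inference, and the power figure is conditional. Nothing in the document suggests that any estimate, test or conclusion of the trial would change because of this.

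**What to change.** Make the sample size statement true in both places where it appears, Sample size justification and the Methods paragraph of the Abstract. Either of two changes does this.

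1. Correct the minimum to 28 / (1 − 0.20) = 35 per group and 70 in total. This costs one more participant per group and still fits five subgroups of six or seven.
2. Keep 34 and 68 and reword. State either that 34 per group tolerates the loss of at most 6 (17.6%), or that about 27 per group would remain at 20% attrition, with power slightly below 80%. If a power value is quoted, recompute it with the method that produced the 28 and name that method. The 78.5% above holds only for the assumed t-test. This costs one sentence and no extra participants.

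In either case, print the inflation formula so that the step can be checked.

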### Participant allocation

Two groups will be under study for this quasi-experiment: the intervention group and the control group. The recruited participants will be allocated into one of the two groups based on their geographical location to ensure participants’ convenience when participating in the intervention activities. The participants in the intervention will be further divided into five subgroups, each consisting of six to seven members based on their peer connectivity. The non-random allocation considers familiarity and peer support, which are expected to lead to higher engagement levels in the intervention activities, promoting better adherence to the intervention and potentially more significant lifestyle behavioural changes.

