### Statistical analysis

Data analyses will be conducted using the Statistical Package for the Social Sciences (SPSS) version 28.0 (IBM Corp., USA). Nutrient intakes from 24-hour dietary recalls will be analysed with Nutritionist Pro software (Axxya Systems, USA) to yield total energy, macronutrient and micronutrient intakes, then transferred to SPSS for analysis. Other data obtained from the assessment will be directly entered and analysed using the SPSS software. Descriptive statistics will be calculated for each variable. Continuous variables will be expressed as a mean with standard deviation (SD) or median with interquartile range. Frequencies and percentages will be obtained for categorical variables. Independent t-test or equivalent will determine differences between the study groups for continuous variables. McNemar and Chi-Square tests will be performed for similar comparisons for categorical variables. Comparison of changes in outcome measures at T0, T1 and T2 between study groups will be analysed using two-way repeated measures analysis of covariance (ANCOVA) to adjust for any baseline differences in key variables. Correlation analyses will be performed between satisfaction and adherence, with changes in outcome measures at T1 and T2.

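### The intervention arm works in five peer groups, but the named tests and the sample size treat all participants as independent

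*Protocol article*

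**What the plan says.** Participant allocation in the protocol article makes two structural choices. Participants are "allocated into one of the two groups based on their geographical location". The intervention arm is then split: "The participants in the intervention will be further divided into five subgroups, each consisting of six to seven members based on their peer connectivity". The Control group section withholds peer support from controls, so they have no comparable grouping. The design is therefore partially nested: five clusters in one arm and single individuals in the other.

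Sample size justification rests on an effect size of 0.25, 80% power, two-sided 5% and 20% attrition. It concludes that "the minimum number of participants required in each intervention and control group is 28", with 34 per arm to be recruited. No ICC or design effect enters.

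Statistical analysis names the independent t-test or equivalent, McNemar and chi-square tests, and correlations. For the main comparison, changes over T0, T1 and T2 "will be analysed using two-way repeated measures analysis of covariance (ANCOVA"), with adjustment for baseline differences. The repeated-measures part handles correlation within a person. No named method handles correlation between members of a peer group.

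**The concern.** The peer groups are formed from connected people, and the program works through them: the allocation section expects familiarity and peer support to raise engagement, adherence and behaviour change. Some similarity of outcome within groups is thus part of the intended mechanism. A test that counts the members of one group as independent overstates the information in the intervention arm whenever the within-group correlation is positive. P-values and confidence intervals for the primary outcome, change in the Framingham risk score (FRS), would then be too optimistic, as would those for secondary outcomes with the same property. The stated 80% power would also carry no allowance for the design. If group membership is not recorded, the analysis cannot be corrected afterwards.

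**Working it through.** **Inputs from the article.** 28 evaluable per arm; five peer groups, so 28/5 = 5.6 completers per group (34/5 = 6.8 recruited); two-sided 5%; 80% power; effect size 0.25; three assessments.

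**Assumed.** ICC from 0.01 to 0.20; clustering in the intervention arm only.

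**1. The plan's own figure.** The article names no test, effect metric or correlation between visits, so 28 per arm cannot be uniquely reproduced. Reading 0.25 as Cohen's f:
- Group-by-time interaction, three visits, assumed visit correlation 0.5: noncentrality λ = N·f²·3/(1 − 0.5). A total of 28 gives λ = 10.5 and power 81.2%. A total of 56 gives λ = 21 and power 98.7%.
- Same test, visit correlation 0: 54 in total are needed (27 per arm), and 56 give 82.4%.
- Single-time ANOVA: 128 in total are needed, and 56 give 45%.

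**2. Variance inflation.** In the intervention arm, DE = 1 + (5.6 − 1)·ICC. With equal arms and unclustered controls, the variance of the between-arm difference rises by R = (1 + DE)/2.

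**3. Type I error of the unadjusted test.** α = 2[1 − Φ(1.96/√R)].

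**4. Power at face value** (28 per arm gives exactly 80% without clustering). Power = Φ((1.96 + 0.84)/√R − 1.96).

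| ICC | DE | R | True α | Power |
|---|---|---|---|---|
| 0.01 | 1.046 | 1.023 | 5.3% | 79.1% |
| 0.02 | 1.092 | 1.046 | 5.5% | 78.2% |
| 0.05 | 1.230 | 1.115 | 6.3% | 75.6% |
| 0.10 | 1.460 | 1.230 | 7.7% | 71.4% |
| 0.20 | 1.920 | 1.460 | 10.5% | 64.0% |

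Simulation with groups of 6, 6, 6, 5 and 5 against 28 controls agrees: about 6.4%, 7.6% and 10.5% type I error at ICC 0.05, 0.10 and 0.20.

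**5. Small-sample degrees of freedom.** A valid test must estimate between-group variance from five groups. Take variance DE/28 on 4 df in the intervention arm and 1/28 on 27 df among controls, combined by Satterthwaite. At ICC 0 the df are (2/28)²/[(1/28)²/4 + (1/28)²/27] = 13.9. The standardised difference that 28 per arm detects with 80% power is 0.76 SD, back-solved and not in the article. Power for that difference is about 75% at ICC 0, 69% at 0.05, 64% at 0.10 and 55% at 0.20. About 5 points of the fall are therefore the cost of having five groups, not of correlated outcomes.

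**6. The interaction reading under clustering.** Replace N = 56 by 56/R, with visit correlation 0.5: power is 97.6%, 96.2% and 92.4% at ICC 0.05, 0.10 and 0.20. Taking this basis through the five-group test of step 5 gives about 95%, 92% and 87%. With visit correlation 0, replacing N by 56/R gives 77.7% at ICC 0.05 and 73.1% at 0.10.

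**The case against.** **Power.** A reader might infer that the trial does not deliver 80% power. The article does not support this as a flat statement. On the interaction reading with visit correlation 0.5, power stays above 80% at every ICC shown. On a single-time reading it is about 45% before any clustering. Only the face-value reading, which leaves no slack, makes every positive ICC push power below 80%. This objection stands, and the power loss is conditional.

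**Size of the ICC.** None is given. Analysing change in FRS and adjusting for baseline may remove some shared variation, and at ICC 0.01-0.02 the type I error is only 5.3-5.5%. This stands as a limit on size, not on direction.

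**How groups are run.** It is tempting to say that each subgroup has its own leader and its own WhatsApp chat. The Intervention group section refers only to peer leaders and a WhatsApp group, so one chat for the whole arm is equally consistent. The point needs only the five connected groups, which are explicit.

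**Locality.** A reader might go further and treat each arm as a single area, which gives much larger error rates. The article does not state how many areas each arm covers. If it is one, the problem is confounding, which no model can remove. The Discussion already discloses that allocation by location may introduce selection bias. Those error rates are not relied on here.

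**Condensed article.** A fuller analysis plan could add a peer-group term. But the article names the tests and the model rather than deferring them, and none of those named has such a term.

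**Conclusion.** The point holds in conditional form. The delivery structure is explicit, and neither the named between-group tests nor the sample size allows for it. Given any positive within-group correlation, the unadjusted tests are anti-conservative whichever power basis was used. The excess is small at ICC 0.01-0.02 and reaches about 7.6% true type I error at 0.10 and 10.5% at 0.20. These figures rest on 28 completers per arm, near-equal groups, clustering in the intervention arm only and an assumed ICC. The 80% power makes no allowance for the design, but whether true power falls below 80% cannot be settled until the powered test, effect metric and visit correlation are named.

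**What to change.** 1. Record each intervention participant's peer group. Analyse FRS and the other continuous outcomes with a partially nested linear mixed model: a random peer-group effect in the intervention arm only, each control as their own cluster, the repeated visits kept within person, and Satterthwaite or Kenward-Roger degrees of freedom. Use the analogous model for categorical outcomes.
2. Restate the power for the five-group structure over an assumed ICC range, for example 0.01 to 0.10. Name the test, effect metric and visit correlation on which it rests.
3. Record a locality code for every participant. If each arm is one area, state that area and treatment cannot be separated by any model.

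The cost is revised analysis wording and two extra data fields (peer group and locality). The model can be run in the planned software, and no participants are added. The downside is a wider confidence interval and a lower stated power; with only five groups, some of that cost arises even if the ICC is zero.

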#### Control group

Participants in the control group will receive personalised lifestyle advice from a registered nutritionist at baseline, and standard printed materials on CVD prevention and healthy lifestyle habits. The control group participants will only be contacted for re-assessment at T1 and T2. The intervention content of MYCardio-PEER and peer support will not be provided to the control group.

#### Intervention group

The participants in the intervention group will undergo the MYCardio-PEER program for eight weeks, which will be led by trained peer leaders. Participants will be added to a WhatsApp group whereby bite-sized educational videos, infographic posters, and interactive activities that cover knowledge, nutrition and lifestyle behaviours for CVD prevention will be shared. Besides that, the peer leaders will also organise physical meeting sessions at convenient locations with group members, including an exercise club and healthy food preparation demonstration.

### Intervention program

The elements of the MYCardio-PEER intervention program are developed based on the current evidence on peer-led lifestyle intervention for primary prevention of CVD (Lim et al., 2024), clinical practice guidelines on primary and secondary prevention of CVD (MOH, 2017) and Malaysian Dietary Guidelines (NCCFN, 2021). The behaviour change objectives, intervention strategies and delivery methods are developed using the Integrated Theory of Health Behaviour Change (Ryan, 2009). The conceptual framework of the intervention program is presented in Fig. 2. The details of the program development will be described in subsequent publication. Briefly, MYCardio-PEER intervention is expected to improve the knowledge and beliefs related to CVD, self-regulation skills and ability, and provide peer support. This, in turn, improves CVD risk factors and lifestyle behaviours, and eventually improves cardiovascular health.

**Figure 2. f2:**
[figure not shown]
Conceptual framework of the intervention program.

The peer leaders will distribute evidence-based bite-sized educational videos and infographic posters developed for MYCardio-PEER via a WhatsApp group chat platform each week. These multimedia materials will comprehensively address topics related to knowledge dissemination, nutritional guidance, and lifestyle modifications pertinent to CVD prevention. The general topics and objectives of digital content are presented in Table 2. Within the week, peer leaders will also introduce interactive activities through the group chat or organise face-to-face sessions to enhance learning and practice behaviours. In the group chat, participants will be encouraged to pose questions, challenges, or experience sharing relevant to reducing CVD risk.

**Table 2. tbl2:** Topics and objectives of MYCardio-PEER intervention by week

Week	Topic	Objectives
1	Are you at risk of heart disease?	Identify the modifiable risk factors associated with CVD
2	Say YES to physical activity	Encourage the adoption of an active lifestyle
3	How to maintain a healthy weight?	Achieve and maintain a healthy body weight
4	Control your blood pressure	Obtain practical diet and lifestyle strategies for controlling blood pressure
5	Keep your cholesterol in check	Obtain practical diet and lifestyle strategies for maintaining healthy cholesterol levels
6	The not-so-sweet truths	Obtain practical diet and lifestyle strategies for maintaining healthy blood glucose levels
7	Enjoy living smoke-&-stress-free	Encourage a smoke-free lifestyle Enhance stress management
8	Practical tips for heart-healthy meals	Encourage the adoption of healthy eating habits that align with dietary guidelines for cardiovascular health

### Outcome measures

The primary outcome of this study is the change in FRS, which is calculated based on age, sex, levels of high-density lipoprotein cholesterol (HDL-C) and total cholesterol, systolic blood pressure (SBP), smoking habit and the presence of diabetes. This risk calculator has been validated in the Malaysian local population and is recommended for assessing and managing the global risk of individuals in primary prevention of cardiovascular disease (CVD) (MOH, 2017).

The secondary outcomes include changes in body weight, body mass index (BMI), waist circumference, hip circumference, fasting blood glucose (FBG), low-density lipoprotein cholesterol (LDL-C), triglycerides (TG) levels, diastolic blood pressure (DBP), Medication Taking and Understanding Self-efficacy (MUSE), attitudes and beliefs about CVD, physical activity level, lifestyle habits (smoking, alcohol consumption and sleep duration), stress level, edible oil use and dietary intakes.

A process evaluation will be conducted at T1 among the intervention participants to assess their adherence to the program and satisfaction towards content and peer leadership.

### Data collection

Study researchers will administer a pretested, structured questionnaire in both Malay and English language to collect data of the outcome measures at T0, T1 and T2. Sociodemographic data and medical history will be collected at T0 only. At T1, the program feedback form and questionnaire on content satisfaction will be administered among the intervention participants.

#### Clinical measures

The levels of total cholesterol, HDL-C, LDL-C and TG will be measured using the CardioChek PA analyser (PTS Diagnostics, USA). Blood pressure will be measured using the automatic blood pressure monitor (HEM-7120, Omron Healthcare, Japan). Fasting blood glucose will be assessed using the GlucoSure Autocode metre (Apex Biotechnology Corp, Taiwan). All measurements will be taken based on the standard procedures. Blood pressure will be measured twice to get the average readings.

